### 2.10. Statistical Analysis

The statistical analysis will consist of three phases. The first will consist of testing the effectiveness of randomization in creating three comparable groups of participants with HFpEF, exploring the presence of outliers, and testing the degree of adjustment of the main variables to the normal distribution.

In the second phase, ANCOVA models will be used (baseline and 3 months) in which the dependent variables will be each outcome variable, and the intervention will be the fixed effect (2 = CE, 1 = HIIT and 0 = GC), adjusted for baseline, age, sex and socioeconomic status. The results will be expressed as absolute differences in changes in variables between baseline and final measurements (95% confidence interval (95% CI)). Bonferroni post hoc tests will be performed for paired comparisons.

In the third phase, a comparison of CE, HIIT and CG will be performed using the propensity score matching method to take into account covariate imbalance in baseline measurements between subjects. The propensity score estimates the effect of the intervention using a causal inference model, which explains what would have happened if all subjects in the intervention and control groups had the same characteristics at baseline. Each subject is matched to a subject with similar characteristics using a 0.40 caliper using the psmatch2 command.

All analyses will be performed by INTENT TO TREAT, keeping subjects in the originally assigned intervention or control group, regardless of the number of physical activity program sessions attended, and considering the CONSORT.

The results with *p* < 0.05 will be considered statistically significant. The analysis will be performed with the STATA16 statistical package. 

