To date, several systematic reviews and meta-analyses of randomized clinical trials (RCTs) have suggested that physical exercise can lead to important changes in different parameters of exercise capacity, such as fitness as measured by VO2max and diastolic function as measured by echocardiographic parameters [13,14,15,16,17,18,19,20,21]. However, most of these systematic reviews and meta-analyses analyzed all types of exercise together and did not explore the effect on endothelial function and arterial stiffness. In addition, there are currently eleven published RCTs [22,23,24,25,26,27,28,29,30,31,32] on the effect of physical exercise on different parameters of exercise capacity, mainly VO2max. Most of these compare the effect of moderate aerobic exercise versus a control group, while two clinical trials and one pilot study compare moderate aerobic exercise versus HIIT (with one of these studies including a control group) and a single pilot study comparing CE versus a control group. Only two studies analyzed the effect of moderate aerobic exercise on endothelial function and arterial stiffness [28,29]. Recently, a network meta-analysis compared the effect of aerobic exercise, CE and HIIT, supporting the well-known effect of aerobic exercise but showing promising findings for CE and HIIT not only on VO2max but also on diastolic function [33].

Due to the lack of studies analyzing the effect of CE and HIIT and their impact, not only on improving exercise capacity and cardiac function but also on endothelial function and arterial stiffness, in participants with HFpEF, this RCT will be conducted to (1) compare the efficacy of CE and HIIT on exercise capacity, diastolic function, endothelial function and arterial stiffness in patients with HFpEF and (2) to compare the efficacy of CE and HIIT on QoL in participants with HFpEF.

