### 2.4. Randomization

After informed consent and screening, participants will be randomly distributed (1:1:1) using EPIDAT 4.2 software (Figure 1) into three groups: group 1, CE (continuous aerobic exercise with moderate intensity strength exercises); group 2, HIIT; and group 3, control group (CG).

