### 2.9. Sample Size Calculation

The sample size calculation is based on data from the RCT by Mueller et al. [31] which reveals that 21 participants per group would provide 80% power at *p* < 0.05 to detect a statistically significant result for VO2max, the primary outcome. Considering the three groups (CE, HIIT and GC) and a dropout rate of 20%, a total of 72 participants will be recruited.

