## 4. Discussion

The primary objective of this study will be to compare the effectiveness of CE and HIIT on exercise capacity, diastolic function, endothelial function, and arterial stiffness in participants with HFpEF, and the secondary objective of this study will be to compare the effectiveness CE and HIIT on QoL in participants with HFpEF.

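### The stated 80% power is set at p < 0.05 with no allowance for multiplicity, so it is not shown to apply to the Bonferroni-adjusted pairwise tests or to the CE v HIIT comparison

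*Protocol article*

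**What the plan says.** Section 2.9 takes the sample size from one earlier RCT: "21 participants per group would provide 80% power" at p < 0.05 for VO2max, which it calls the primary outcome. It gives no effect, SD, contrast, sidedness or test, and no adjustment for several comparisons. It continues: "Considering the three groups (CE, HIIT and GC) and a dropout rate of 20%, a total of 72 participants will be recruited". Section 2.4 allocates 1:1:1.

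Section 2.10 specifies ANCOVA with a three-level group factor, adjusted for baseline, age, sex and socioeconomic status. Of the pairs it says "Bonferroni post hoc tests will be performed for paired comparisons", and of the threshold, "The results with *p* < 0.05 will be considered statistically significant".

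The Discussion opens with "The primary objective of this study will be to compare the effectiveness of CE and HIIT on exercise capacity" and further outcomes, and the last paragraph of the Introduction words the first aim in the same way. The Introduction describes the eleven published RCTs, among which the planning RCT is cited. Most compare moderate aerobic exercise with control, three compare it with HIIT, and there is "a single pilot study comparing CE versus a control group". It describes none that compares CE with HIIT.

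**The concern.** The sizing and the analysis refer to different tests. With three arms there are three pairs, so a Bonferroni test at an overall 0.05 needs p < 0.05/3 = 0.0167 for each pair. Power of 80% at 0.05 is not power of 80% at 0.0167. Both statements are fixed in the protocol itself, so this is not detail left to a separate analysis plan.

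The comparison named as the primary objective is also not one for which the planning source, as the protocol describes the literature, could have supplied an effect. If readers take the 80% to cover CE v HIIT, a non-significant result could be given more weight than the trial can bear. Neither type I error nor bias is affected. What is at stake is whether the stated power is correct and how a null result is read.

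**Working it through.** **Inputs.** From 2.9: 21 per group, 80% power, 0.05, 72 recruited, 20% dropout. From 2.10: Bonferroni for pairs. From 2.4: equal allocation. Assumed: two-sided testing, three pairs, SD = 1.

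**1. The plan's own figure.** The 80% cannot be reproduced forwards, because no effect or SD is given. Solving backwards for an unadjusted two-sided two-group test with n = 21:
- Normal approximation: d = (1.960 + 0.842) × √(2/21) = 0.865.
- Noncentral t, 40 df: d = 0.886.

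**2. Power of that d at 0.05/3.** Two-sample t, noncentrality d × √(n/2):

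| n per arm | alpha 0.05 | alpha 0.0167 |
|---|---|---|
| 21 | 80.0% | 64.6% |
| 19 | 75.7% | 59.0% |

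The normal approximation gives 65.8% and 60.7% in the last column. Restoring 80% at 0.0167 takes 29 per arm. With 20% loss that is 29/0.8 = 36.25, so 37 per arm and 111 in total.

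**3. The number after dropout, a separate matter.** 72/3 = 24 per arm, and 24 × 0.8 = 19.2. Keeping 63 evaluable would need 63/0.8 = 78.75, so 79 in total, or 27 × 3 = 81 in equal arms. The planned 72 covers a loss of 1 − 63/72 = 12.5%. Without Bonferroni, this alone takes power from 80% to about 76%.

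**4. How far the 65% depends on the assumed basis.**
- *Raw SD in the sizing, baseline-adjusted analysis.* The residual SD is multiplied by √(1 − r²). At 0.0167, power with 21 and 19 per arm is 69% and 64% for r = 0.3, 79% and 74% for r = 0.5, and 86% and 81% for r = 0.6. These correlations are assumptions. If the planning SD was already a change-score or adjusted SD, the gain is smaller or absent.
- *Overall three-group F-test.* f = 0.40 with 21 per group gives 79.8%, so this basis fits the 21 as well. At 0.0167 the largest pairwise contrast then has about 62% power (means 0, d, d) to 76% (means 0, d/2, d), and 56-71% with 19 per arm.
- *Two pairs only.* At 0.025, about 71%.
- *One-sided sizing, two-sided Bonferroni tests.* About 54%.

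**5. CE v HIIT.** The article gives no expected difference, so only a range can be shown, for 21 per arm and as a fraction of the back-solved d (t-test):

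| CE v HIIT difference (assumption) | alpha 0.05 | alpha 0.0167 |
|---|---|---|
| d | 80% | 65% |
| 0.75d | 56% | 38% |
| 0.5d | 29% | 16% |

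The half-width of an unadjusted 95% CI is 2.02 × √(2/21) = 0.62 SD with 21 per arm and 2.03 × √(2/19) = 0.66 SD with 19, before any gain from baseline adjustment.

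**6. The closed alternative.** With exactly three groups, an overall test at 0.05 followed, only if significant, by each pair at 0.05 is a closed procedure. Simulated with pooled variance and 21 per arm, power for the largest exercise v control contrast is:
- both exercise arms at d: 76% closed, 66% Bonferroni;
- one arm at d, the other at d/2: 70% closed, 66% Bonferroni.

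With 19 per arm and both exercise arms at d, the figures are 71% and about 60%. When only control differs, the false-positive rate for CE v HIIT is 4.9%.

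**The case against.** The strongest reply is that the power loss cannot be calculated from this article. The d of 0.886 exists only if the 21 came from an unadjusted two-group test. An overall F-test is an ordinary basis for a three-arm ANCOVA and fits equally well. The calculation in step 2 also ignores the covariate adjustment that section 2.10 specifies. With a raw planning SD and a baseline correlation of about 0.5, most of the Bonferroni loss is recovered at 21 per arm. This stands. A reader might infer that the trial's actual power is 65%, or 59%, and the documents do not support so firm a figure.

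Three further points stand:
- The fall from about 65% to 59% comes from the dropout arithmetic and not from Bonferroni.
- It is tempting to say that power for CE v HIIT is far lower, because two active programmes should differ by less than exercise and control. That is plausible, but no figure in the article supports it. The supportable statement is that no such difference is given.
- Bonferroni is a valid, prespecified control of family-wise error, so replacing it corrects no error.

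The objective is also less sharp than its wording suggests. The Abstract randomises to a control arm to evaluate the exercise programmes, and nothing in the article plans to read non-significance as equality.

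What the reply does not remove is the mismatch itself. Section 2.9 does not say that multiplicity was allowed for or that covariate gain was relied on, and covariate gain would not supply a CE v HIIT effect.

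**Conclusion.** The point holds in conditional form. The stated 80% at p < 0.05 is not shown to apply to the pairwise tests of section 2.10, nor to CE v HIIT.

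On the simplest reading (unadjusted, two-sided, two-group sizing; three pairs), power per contrast is about 65% at 21 per arm. The other bases in step 4 move this down or up, to about 79% at a baseline correlation of 0.5 and beyond that at higher correlations, and the article does not select among them. Combined with the separate shortfall in the total of 72, the simplest reading gives about 59%.

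For CE v HIIT no basis for any power claim is shown. The 29% unadjusted and 16% under Bonferroni illustrate an assumed half effect and are not estimates of what the trial has.

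**What to change.** 1. In 2.9, state the contrast, effect, SD, sidedness and test behind the 21. Restate the power for the adjusted pairwise test at the number left after dropout, and reconcile the 72 with the 20%. If baseline adjustment is relied on, give the assumed correlation.
2. State that the power claim does not cover CE v HIIT. Report that contrast as an estimate with its 95% CI (half-width about 0.6 SD unadjusted), and say that non-significance will not be read as equal efficacy.
3. As an optional improvement, replace Bonferroni for VO2max by the closed procedure: the overall ANCOVA arm test at 0.05 and, only if it is significant, each pairwise contrast at 0.05. This keeps family-wise control and adds about 4 to 10 points of power for the largest exercise v control contrast.

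Items 1 and 2 cost wording and probably a less favourable stated power. Raising recruitment is needed only if the sponsor wants to restore 80%. Item 3 needs no extra participants. Its drawback is that simultaneous confidence intervals are less direct than with Bonferroni, which matters because section 2.10 reports differences with 95% CIs.

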### 2.11. Participation of Subjects with HFpEF in Research

The design and purpose of the RCT will be exposed to an advisory group of subjects with HF-PEF from the Cuenca I, II and III health centers of Cuenca. This advisory group will meet periodically during the duration of the study, especially for the drafting of clinical implications in the reports and conclusions. In addition, they will participate in the design of dissemination material after being informed of the findings and conclusions and will contribute to the dissemination plan.

## 3. Results

The results will be published as a peer-reviewed article.

## 4. Discussion

The primary objective of this study will be to compare the effectiveness of CE and HIIT on exercise capacity, diastolic function, endothelial function, and arterial stiffness in participants with HFpEF, and the secondary objective of this study will be to compare the effectiveness CE and HIIT on QoL in participants with HFpEF.

### 4.1. HFpEF and Exercise Capacity

One of the hallmarks of HFpEF is severe impairment of exercise capacity. Exercise intolerance, manifested by symptoms of exertional dyspnea and fatigue, impairs QoL and is therefore one of the main consequences for participants with HFpEF. Furthermore, reduced exercise capacity in HFpEF is associated with worse clinical outcomes [36]. Studies to date have used a variety of techniques to examine the mechanisms of exercise intolerance in HFpEF and have variably reported the contribution of central (e.g., HR, stroke volume, filling pressures) and peripheral (e.g., VO2max, body mass index, renal function) factors.

### 4.2. HFpEF and Diastolic Function

HFpEF is characterized by abnormal diastolic function: there is an increase in left ventricular stiffness, leading to decreased left ventricular relaxation during diastole, with a consequent increase in pressure and/or impaired filling. There is evidence that long-term aerobic exercise may improve diastolic function because this exercise attenuates left ventricular remodeling due to a reduction in vasoconstrictor neurohormones or a decrease in hemodynamic load [17]. However, this evidence has not been demonstrated in participants with HFpEF, nor has it been analyzed with other types of exercise.

### 4.3. HFpEF and Endothelial Function

The relationship between endothelial dysfunction and HF has been well established in many studies [37]. Endothelial function is not only closely associated with HFpEF but also strongly predicts events in participants with HFpEF [38]. This is because endothelial cells (1) participate in antioxidant and anti-inflammatory activities in arteries; (2) interact with the extracellular matrix (elastic and collagen fibers) to regulate vascular elasticity; and (3) directly affect vascular tone by synthesizing and releasing nitric oxide [39]. Endothelial function plays an important role in arterial stiffness and HFpEF.

### 4.4. HFpEF and Arterial Stiffness

The change in arterial hemodynamics plays a key role in HFpEF. Arterial stiffness is a determinant of pulsatile afterload, which is one of the two main components of arterial load. Arterial wave reflections increase with arterial stiffness, leading to increased mid and late systolic load and subsequent left ventricular abnormalities, such as concentric remodeling, myocardial fibrosis, contractile dysfunction, and reduced ejection duration. These changes further contribute to the increase in mid and late systolic load, resulting in a vicious cycle [40]. Because of the contribution of arterial stiffness in HFpEF, therapies targeting arterial stiffness may be useful in the treatment of this disease. To date, aerobic exercise, CE and HIIT have been shown to be the most effective in reducing arterial stiffness [41]; however, these findings have not yet been demonstrated in subjects with HFpEF.

### 4.5. HFpEF and QoL

Given the paucity of treatments that decrease mortality in HFpEF, there is interest in focusing on possible treatments to improve QoL in these patients [42], taking into account the multidimensional concept of QoL (physical and psychological dimensions) [43]. Patients with HFpEF are usually elderly and their main chronic symptom is severe exercise intolerance which reduces their QoL [16]. Functional capacity and activities of daily living correlate more strongly with QoL impairment in this type of patient [42], showing a lower QoL in the physical dimension compared with other chronic patients [43]. Previous meta-analyses and several ECAs have shown an improvement in exercise capacity and QoL after training in patients with HF [26,43,44].

## 5. Conclusions

With this study, we will provide evidence to healthcare professionals on the efficacy of CE and HIIT in improving exercise capacity, diastolic function, endothelial function and arterial stiffness in participants with HFpEF, as well as improving QoL, considered as a therapeutic goal for these patients. Furthermore, taking into account the increasing prevalence of participants with HF, it is plausible that the clinical importance of HF will increase in the coming years. Therefore, the management of HF is a major challenge for healthcare systems, where it would be important to consider the prescription of physical exercise as a complementary nonpharmacological treatment in this type of patient.

## Figures and Tables

**Figure 1 jcm-12-03535-f001:**
[figure not shown]
Combined exercise (group 1), high intensity interval training (group 2) and control group protocols (group 3).

**Figure 2 jcm-12-03535-f002:**
[figure not shown]
Flow chart for participant inclusion and follow-up: screening, inclusion and exclusion, randomization, baseline testing, and testing after follow-up.

**Table 1 jcm-12-03535-t001:** Inclusion and exclusion criteria.

Inclusion Criteria	Exclusion Criteria
1. HFpEF (diagnosis according to ESC 2021 criteria): a. Signs and symptoms of HF. b. LVEF ≥ 50%. c. Objective evidence of cardiac structural and/or functional abnormalities consistent with the presence of left ventricular diastolic dysfunction/elevated left ventricular filling pressures, including elevated natriuretic peptide. 2. Sedentary men and women (structured exercise < 2 × 30 min/week). 3. Age ≥ 40 years. 4. Written informed consent. 5. Clinically stable for ≥6 weeks. 6. Optimal medical treatment for ≥6 weeks.	1. Noncardiac causes of HF symptoms: -Significant valvular or coronary artery disease. -Uncontrolled hypertension or arrhythmias. -Primary cardiomyopathies. 2. Significant pulmonary disease (FEV1 < 50% predicted, GOLD III-IV). 3. Exercise disability or conditions that may interfere with exercise intervention. 4. Myocardial infarction within the last 3 months. 5. Signs of ischemia during maximal cardiopulmonary stress test. 6. Comorbidity (renal failure, cancer, cognitive impariment) that may influence prognosis at 1 year. 7. Participation in another clinical trial.

ESC, European Society of Cardiology; HF, heart failure; HFpEF, heart failure with preserved ejection fraction; LVEF, left ventricular ejection fraction; GOLD, Global Initiative for Chronic Obstructive Lung Disease; FEV1, forced expiratory volume in the first second.

## Data Availability

Not applicable.
